**Quantitative data analysis**

Quantitative data will be analyzed using the R studio statistical package. Univariate descriptive analyses will be carried out (mean or median age, standard deviation and variance will be calculated), percentage frequencies of the following variables: tests requested, doctors/laboratory technicians who adhered to the intervention, chi-square to check for associations between the intervention/test and the variables (level of education of the professional, availability of the test, severity of the disease and gender) and logistic regression to estimate the relationship between adherence to the test and factors severity of the disease, work overload in the US/laboratory, level of education of the professional, shift, gender, availability of laboratory services.

A Likert scale will be used to assess the level of satisfaction of all those involved in the intervention (doctors and laboratory technicians) during the study period. And the frequencies of the information obtained will be calculated.

The results will be described and presented in tables and graphs using the Microsoft Excel program. A p-value of <0.05 will be considered significant.

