The data will be analysed using the R studio statistical package. The frequencies of the variables (number of tests requested with and without feedback, number of trained professionals) will be calculated and the frequencies will be compared using the Chi-square test.

The correlation between (number of professionals trained and number of tests requested) will be determined; the Odds Ratio (OR) will be estimated using regression: services covered/improved (dependent variable) and independent variables: professional trained, years of practice, level of education of the professional; age, gender.

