# Evaluation of the RE-AIM-based implementation of the technique of laboratory diagnosis of cryptococcosis using the China ink method in urine as a point of care in southern Mozambique

This is a cross-sectional quantitative study aimed at measuring the contribution of the diagnosis introduced (intervention effect) in the six hospitals (MCH, MGH, JMGH, MPH, XPH and CHC) over three months. Sampling will be non-probabilistic, intentional with regard to the participants (healthcare professionals) and by convenience concerning the study sites.

In the Implementation Evaluation Phase (Post-implementation), during three months the implementation will be evaluated using the RE-AIM conceptual framework with five domains reach (comprehensiveness), effectiveness, adoption (acceptability and representativeness), implementation and maintenance (sustainability) of the intervention in the hospitals. Data collection will be based on previously prepared questionnaires and standardized scripts coupled to the REDCap platform loaded onto the tablet.

- Reach will be calculated through the proportion of individuals covered by the intervention (clinicians and laboratory technicians).
- Efficacy will be assessed by checking laboratory and clinical results, time to diagnosis and satisfaction of health professionals.

The study includes an evaluation at the beginning (baseline) pre-implementation and at the end post-implementation, where laboratory and clinical results, time to diagnosis and satisfaction of health professionals will be verified at both times. The efficacy of the intervention will therefore be evaluated before and after implementation. WHO recommendations will be consulted, which recommend screening and treatment to prevent complications from a cryptococcal infection. The test to be implemented will contribute to starting treatment on the same day as the consultation and based on the aetiological diagnosis.

- Adoption will be explored through the representativeness of the services that have adopted the implementation including sample flow, laboratory processing and feedback, use of scripts drawn up and made available during the intervention.
- A Likert scale will also be used to analyze the satisfaction of all health professionals covered by the intervention during the study period (clinicians and laboratory technicians).

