- During implementation, the fidelity of health professionals in relation to the diagnosis, care and treatment of cryptococcosis based on documented observation will be assessed.
- Maintenance (sustainability) will be assessed based on the simplicity of the intervention (laboratory diagnostic technique for cryptococcosis using urine), the workflow and the cost of the test implemented.

The data obtained in this study will be entered into the R studio statistical package, where the following analyses will be performed: Descriptive analysis (calculate frequencies, mean and variance), Chi-square to compare frequencies and multivariate regression to estimate the “Odds Ratio” (OR).

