**QUESTIONÁRIO**

**Código ___ ___ ___/_______/_____/202___**

**AVALIAÇÃO DA INTERVENÇÃO**

**(Clinico)**

1. **As ferramentas disponibilizadas no treino são mais esclarecedores no âmbito de diagnóstico e tratamento da criptococose**

Concordo fortemente Concordo Neutro Descordo Descordo fortemente

1. **A intervenção é uma alternativa recomendável para triagem laboratorial da Criptococose**

Concordo fortemente Concordo Neutro Descordo Descordo fortemente

1. **Desde a sua implementação o teste da tinta-da-China a partir da urina esteve sempre disponível no Hospital**

Concordo fortemente Concordo Neutro Descordo Descordo fortemente

1. **Qualidade dos serviços melhorou com o novo diagnóstico laboratorial**

Concordo fortemente Concordo Neutro Descordo Descordo fortemente

1. **Pode-se estimar a percentagem de pacientes beneficiados pela intervenção em:**

 100%  80 – 99% 50 – 79%  <50%

1. **Avalie a sua satisfação em relação ao diagnostico laboratorial com a técnica da tinta da China usando a urina**

Muito satisfeito Satisfeito Neutro insatisfeito Muito insatisfeito

1. **Avalie a sua satisfação em relação a disponibilidade do pessoal do laboratório quando você tenta contatá-los?**

Muito satisfeito Satisfeito Neutro insatisfeito Muito insatisfeito

1. **Avalie a sua satisfação em relação ao tempo de resposta do laboratório**

Muito satisfeito Satisfeito Neutro insatisfeito Muito insatisfeito

1. **Avalie a sua satisfação em relação ao formulário de solicitação dos enxames laboratoriais**

Muito satisfeito Satisfeito Neutro insatisfeito Muito insatisfeito

1. **Avalie a sua satisfação em relação a clareza, legibilidade e integridade do resultado do laboratório relatório?**

Muito satisfeito Satisfeito Neutro insatisfeito Muito insatisfeito

1. **A qualidade do diagnóstico foi consistente em todos os turnos? (horário de trabalho, fim de semana, feriado, plantão noturno)**

Concordo fortemente Concordo Neutro Descordo Descordo fortemente

1. **Na sua opinião em qual turno, a qualidade do serviço do laboratório foi comprometida?**

Horário de trabalho Fim de semana Feriado Plantão noturno NA

1. **O número de pacientes internados devido a complicações associadas a meningite criptocócica reduziu com a introdução da nova abordagem do diagnóstico**

Concordo fortemente Concordo Neutro Descordo Descordo fortemente

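### Staff satisfaction is an efficacy measure recorded on five ordered levels, but the comparison methods stated for that sub-study are chi-square and an odds-ratio regression, neither stated to use the order

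*Protocol*

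**What the plan says.** Section 7.8 (Quantitative data analysis) introduces the scale: "A Likert scale will be used to assess the level of satisfaction of all those involved in the intervention (doctors and laboratory technicians"), over the study period. Its only analysis instruction for that scale is "And the frequencies of the information obtained will be calculated".

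Section 7.9, third sub-study (RE-AIM evaluation), lists satisfaction under efficacy beside laboratory and clinical results and time to diagnosis. It plans a comparison: "time to diagnosis and satisfaction of health professionals will be verified at both times", meaning pre- and post-implementation. For the data of this sub-study it names descriptive analysis, then "Chi-square to compare frequencies and multivariate regression to estimate" an odds ratio.

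Section 7.9, second sub-study, says "the Odds Ratio (OR) will be estimated using regression: services covered/improved (dependent variable"). It gives neither the coding of that variable nor its source.

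Annex V has a clinician form and a laboratory-technician form. Both rate satisfaction on five levels, "Muito satisfeito Satisfeito Neutro insatisfeito Muito insatisfeito", and both include the agreement item "Qualidade dos serviços melhorou com o novo diagnóstico laboratorial", also on five levels.

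Section 7.5 lists the staff to be involved under the qualitative component. No rank or ordinal method is named anywhere in the protocol.

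**The concern.** A chi-square test on a table of two groups by five levels treats very satisfied through very dissatisfied as unordered labels. It spreads its sensitivity over four degrees of freedom, while the question of interest, whether ratings moved up, concerns one direction. Collapsing the scale to two levels keeps the direction but discards information, and how much depends on where the cut falls. With a few dozen staff, either choice can hide a real shift in a measure that the protocol counts as efficacy. A 2 x 5 table is also thin at this size, so the large-sample chi-square approximation is strained.

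**Working it through.** **1. Staff count (section 7.5).** Clinicians: 8 + 4 + 4 + 3 + 3 + 2 = 24. Technicians: 6 hospitals x 2 = 12. Total 36. If the same staff answer before and after, that is 36 per time point.

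**2. No figure to reproduce.** The protocol gives no power, effect size or expected rating distribution for satisfaction. Everything in step 4 therefore rests on assumptions.

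**3. Sparseness of the 2 x 5 table.** The usual guideline allows at most 20% of cells with an expected count below 5.
- *24 versus 12:* the expected count in the smaller row is 12 x (column total / 36). To reach 5, a column needs 5 x 36 / 12 = 15 responses. Three such columns would need 45 responses, more than the 36 available, so at most two qualify. When all five levels are used, at least 3 of 10 cells (30%) fall below 5.
- *36 versus 36:* the expected count is half the column total, so each level needs at least 10 of the 72 responses. Two levels below 10 make 4 of 10 cells (40%) too small. In simulation this guideline failed in about half to nearly all tables, depending on the baseline.

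**4. Power.** Assumptions:
- two-sided alpha 0.05 (the protocol states p < 0.05 without sidedness);
- independent responses, with the before/after groups treated as unpaired;
- a proportional-odds shift;
- baseline ratings, lowest to highest level, either central (10/20/30/30/10%) or favourable (5/10/20/40/25%).

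Example of the shift: the central baseline has 30 + 10 = 40% in the top two levels, odds 0.40 / 0.60 = 0.667. At OR 3 the odds become 2.0, so the proportion is 2 / 3 = 66.7%. The other cut points move in the same way.

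Simulated power, 3,000 to 4,000 runs per cell:

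| Groups | OR | Baseline | Wilcoxon | Five-category chi-square | Top-two split | Loss, five-category | Loss, split |
|---|---|---|---|---|---|---|---|
| 36 v 36 | 2 | central | 36% | 20% | 30% | 16 | 6 |
| 36 v 36 | 3 | central | 71% | 48% | 61% | 23 | 10 |
| 36 v 36 | 3 | favourable | 71% | 46% | 50% | 25 | 21 |
| 24 v 12 | 3 | central | 38% | 17% | 32% | 21 | 6 |
| 24 v 12 | 4 | central | 55% | 28% | 46% | 27 | 9 |
| 24 v 12 | 4 | favourable | 52% | 24% | 30% | 28 | 22 |

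At OR 1 the rejection rates were about 3.4 to 5.8% for these three tests, so the differences are not bought with inflated type I error.

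Over further baselines at OR 2 to 4, with either grouping, the loss of the five-category chi-square against the rank test was roughly 7 to 29 points. The smallest losses came with 24 versus 12 at OR 2. Against the top-two split the loss ran from near zero, when the cut falls near the middle of the responses, to about 23 points.

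**5. Baseline instrument.** Annexes I to IV cover demographics, laboratory situation, clinician interview and clinician practice. None has a Likert satisfaction item. Annex V is a post-intervention form, and several of its items ask about the new test. As annexed, the before/after comparison of satisfaction has nothing on the before side.

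**The case against.** The strongest reply is that the protocol never says satisfaction will be tested by chi-square. The Likert sentence in section 7.8 is descriptive, the chi-square list in that section covers other variables, and the variables and analysis table omits satisfaction. Chi-square reaches satisfaction only through the general sentence closing the third sub-study. This stands as a limit on the point: the frequencies are no error, and a reader who infers that a chi-square on satisfaction is spelled out goes further than the text. But that sub-study does plan a before/after check of satisfaction, and its closing sentence gives the only comparison methods for its data.

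A reader might also infer that service improvement will be cut to yes/no. The documents do not support that. The coding of "will be estimated using regression: services covered/improved (dependent variable") is not given, its link to the Annex V agreement item is not stated, and a proportional-odds model also yields an odds ratio.

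Third, the power figures depend on assumed baselines and effects. The 24 versus 12 contrast between staff groups is illustrative, because the protocol does not plan it for satisfaction. Staff are clustered in six hospitals and may answer twice, which the simulation ignores. All this stands: the figures show direction and rough size, not a fixed loss.

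Finally, test selection is often left to a statistical analysis plan. That would answer a complaint of silence. Here the protocol names its methods, and the named test suits the data poorly.

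**Conclusion.** The point holds in a limited form. Satisfaction is an efficacy measure with five ordered levels and a planned comparison over time, and the comparison methods stated for it are not stated to use the order. With about 36 staff, under the assumptions above, a five-category chi-square gives up roughly 7 to 29 percentage points of power against a rank test and is too sparse for comfort. A top-two split gives up between almost nothing and about 23 points.

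Two stronger conclusions should be avoided. No single loss figure can be attached to this protocol, since it states no effect size or rating distribution. Nor does an ordered analysis make the study well powered: the rank test itself reaches only 36% at OR 2 with 36 versus 36, and 38% at OR 3 with 24 versus 12. The missing baseline satisfaction items limit the before/after comparison whichever test is chosen.

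**What to change.** - In section 7.8 and in the analysis paragraph of the third sub-study, state that wherever Likert items are compared, chi-square is replaced by a Wilcoxon rank-sum test (signed-rank if the same coded person answers twice) or by a proportional-odds model allowing for hospital. Keep the five-level frequency tables.
- State whether before and after answers can be linked. The limitations section calls the questionnaires anonymous, while the confidentiality section assigns each participant an ID.
- In the second sub-study, define how the services covered/improved variable is coded and where it comes from. If it is the Annex V agreement item, analyse it by ordinal logistic regression.
- Put the same satisfaction items in the baseline questionnaires. Those on staff availability, response time and the request form do not mention the new test and could be asked before it. If baseline collection has already passed, describe satisfaction as a post-implementation measure only.

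The analysis changes cost wording only, with the same sample and software. The baseline items add a few questions to existing forms. The small downside is that the proportional-odds assumption has to be inspected.

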## Research questions

# What opportunities exist to implement the point-of-care diagnostic technique for cryptococcosis in the context of care and treatment of cryptococcosis in HIV patients?

# What factors contribute to the reach, efficacy, adoption, implementation, and maintenance of India ink as a point-of-care diagnostic technique for cryptococcosis in the selected hospitals?

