| To evaluate the implementation of the India ink method as a point of care laboratory diagnosis in selected hospitals, based on the RE-AIM conceptual framework. | Number of services and number of providers that adhered to implementation, age, sex, number of samples tested, test availability, initiation of treatment after positive test. | Frequency (professionals who adhered to the intervention, samples tested, services that adhered to the intervention, age and sex. Chi-square compare frequencies Ex: (relationship between characteristics of professionals and the type of test requested);  Multivariate regression to estimate the “Odds Ratio” (OR) of the relationship between adherence to testing (PS) and the variables: severity of the disease, age of the professional, sex, US, availability of services in the laboratory, and feedback |

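### A flat p<0.05 rule over roughly 25 to 35 factor terms would yield about 1.2 to 1.8 false contributing factors if most have no association; the factor analyses should be labelled exploratory

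*Protocol*

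**What the plan says.** The second research question (section 4.1) is "What factors contribute to the reach, efficacy, adoption, implementation, and maintenance of India ink as a point-of-care diagnostic technique for cryptococcosis" in the selected hospitals. The quantitative part of the answer is spread over several places in the protocol.

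- **Quantitative data analysis (within 7.8).** Chi-square tests for "associations between the intervention/test and the variables (level of education of the professional, availability of the test, severity of the disease and gender", and a logistic model for adherence on "factors severity of the disease, work overload in the US/laboratory, level of education of the professional, shift, gender, availability of laboratory services". The section closes with "A p-value of <0.05 will be considered significant".
- **Sub-study 1 (7.9).** Chi-square comparisons of frequencies, followed by the same significance sentence.
- **Sub-study 2 (7.9).** A chi-square comparison, then "The correlation between (number of professionals trained and number of tests requested) will be determined", then a regression for services covered or improved with "independent variables: professional trained, years of practice, level of education of the professional; age, gender".
- **Variables and data analysis plan (table).** Objective 1 has chi-square tests and an independent t-test. Objective 2 has a chi-square test, the correlation and an eight-factor odds-ratio model. Objective 3 has chi-square comparisons, given only by example, and an odds-ratio model for "adherence to testing (PS) and the variables: severity of the disease, age of the professional, sex, US, availability of services in the laboratory, and feedback".

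The significance sentence carries no qualification. No association is singled out as primary, no order of testing is given, and none of these analyses is described as exploratory. The only hypothesis-generating language is in the description of the qualitative thematic analysis.

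**The concern.** A per-test threshold of 0.05 controls the error of one test. Here the same threshold is set for a long list of factors, and the list is the planned quantitative answer to one of the two research questions. Any factor that crosses the line may be called significant. Some are likely to do so by chance, and nothing in the plan lets a reader tell those apart from real contributors.

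The protocol intends its findings to inform the Ministry of Health and foresees expansion to peripheral hospitals (Contribution; Expected results). A chance finding about, say, shift or years of practice could then be presented as a barrier or facilitator worth acting on.

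**Working it through.** The protocol states no family-wise error rate, so there is no figure to reproduce. The check counts the terms and then computes the error rate over a range of counts and correlations.

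**1. Count of terms**

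| Place | Terms | Number |
|---|---|---|
| Quantitative data analysis | 4 chi-square + 6 logistic | 10 |
| Sub-study 2 text | 1 chi-square + 1 correlation + 5 regression | 7 |
| Table, objective 1 | 2 chi-square + 2 t-test | 4 |
| Table, objective 2 | 1 chi-square + 8 regression (correlation already counted) | 9 |
| Table, objective 3 | at least 1 chi-square + 6 regression | 7 |
| Total | | 37 |

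*Upper working count.* The chi-square of test request against feedback appears twice (−1), and the objective 1 t-test may be one comparison (−1): 37 − 2 = 35.

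*Lower working count.* Start again from 37 and remove:
- 3 terms shared by the two adherence models (severity, sex, availability of laboratory services);
- 4 terms shared by the two sub-study 2 models, if these are one model restated (education, years of practice, age, sex);
- 1 repeated chi-square;
- 4 objective 1 tests, which describe baseline practice and do not serve the contributing-factors question.

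37 − 3 − 4 − 1 − 4 = 25. As a check: 9 + 9 regression terms, 6 chi-square tests and 1 correlation = 25.

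**2. Expected false positives if no factor has an association**

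0.05 × 25 = 1.25 and 0.05 × 35 = 1.75. This figure does not depend on how the tests are correlated.

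**3. Chance of at least one false positive**

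Independent tests: 1 − 0.95^k. For k = 25 this is 0.723, for k = 35 it is 0.834. It first exceeds one half at k = 14 (0.512).

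Equally correlated two-sided z-tests with correlation ρ: 1 − E{[Φ((1.96 − √ρ·W)/√(1−ρ)) − Φ((−1.96 − √ρ·W)/√(1−ρ))]^k}, with W standard normal.

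| k | ρ = 0 | ρ = 0.3 | ρ = 0.5 | ρ = 0.8 |
|---|---|---|---|---|
| 10 (general section alone) | 0.40 | 0.35 | 0.29 | 0.17 |
| 25 | 0.72 | 0.61 | 0.47 | 0.24 |
| 30 | 0.79 | 0.66 | 0.51 | 0.26 |
| 35 | 0.83 | 0.71 | 0.54 | 0.27 |

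**4. Check with shared data**

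The four regressions (6 + 6 + 5 + 8 = 25 coefficients) and 8 chi-square tests were fitted to common simulated data with no true association. Sample sizes were 36, 100 and 300; 36 is the number of professionals listed under Sample and Sampling (10 + 6 + 6 + 5 + 5 + 4). Correlations between outcomes were 0, 0.5 and 0.8. The chance of at least one false positive was 0.65 to 0.74 for the 25 coefficients and 0.68 to 0.78 for all 33 tests, with 1.7 to 1.9 false positives on average. The simulation used binary covariates that were mostly independent, and it ignored clustering within the six hospitals.

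**The case against.** **The statistical analysis plan is not shown.** Multiplicity rules are commonly placed there, so the lack of an adjustment in the protocol is not by itself a fault. This stands. The point rests instead on the unqualified rule that the protocol does state, which any later document would have to override.

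**The rule is written in only two places.** Sub-studies 2 and 3 and the table carry no threshold. Extending the sentence to them relies on the general standing of the quantitative section. That is a reasonable reading but an inference, and on the section's own 10 terms the risk is 0.29 to 0.40.

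**The family could be drawn more narrowly.** The three sub-studies have separate objectives. Taken singly, sub-study 1 has 4 tests (0.16 at ρ = 0.5 to 0.19 if independent), the objective 3 row has 7 (0.23 to 0.30), and sub-study 2 has about 15 (0.36 to 0.54). This is a fair alternative, and it lowers the risk for each.

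**Odds ratios are already framed as estimates, and barriers and facilitators are also sought through interviews, questionnaires and equipment lists.** Both are true, and no passage ties p<0.05 to a decision on scale-up. The wording still permits individual factors to be declared significant.

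**A stronger reading is tempting.** A reader might infer that a false contributing factor is more likely than not, or that the plan is bound to report factors that do not exist. The documents support neither without conditions. At ρ = 0.5 the chance is close to one half and falls on either side of it according to the count. Moreover, the assumption of no association is doubtful for some pairs, such as professionals trained against tests requested.

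**Conclusion.** The concern holds in conditional form. The protocol fixes a flat 0.05 rule which, on the natural reading of its general section, covers roughly 25 to 35 factor terms. If most of those factors have no true association, about 1.2 to 1.8 false significant factors are expected. The chance of at least one is 0.72 to 0.83 under independence, 0.61 to 0.71 at ρ = 0.3, and around one half or less at ρ = 0.5 and above.

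This rests on three assumptions: each test holds its own 5% level, most listed factors are null, and the sentence governs the later lists. It does not make the study invalid; it limits what may be concluded from the factor analyses.

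**What to change.** In Quantitative data analysis and in sub-study 1, replace the significance sentence with a statement that all factor analyses (chi-square, t-test, correlation and odds-ratio models) are exploratory, are reported as estimates with 95% confidence intervals, and will not be used to declare factors significant. If p-values are shown, call them nominal. Holm's adjustment within each sub-study is an option, at some loss of power.

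The new text should not reserve p<0.05 for one efficacy comparison, because the protocol defines none: sub-study 3 assesses efficacy through laboratory and clinical results, time to diagnosis and satisfaction.

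The cost is wording only, with no new data and no change in design. The downside is that fewer factors can be called significant.
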